## Abstract

**Background:**

Identifying scalable strategies for assessing fidelity is a key challenge in implementation science. However, for psychosocial interventions, the existing, reliable ways to test treatment fidelity quality are often labor intensive, and less burdensome strategies may not reflect actual clinical practice. Cognitive behavioral therapies (CBTs) provide clinicians with a set of effective core elements to help treat a multitude of disorders, which, evidence suggests, need to be delivered with fidelity to maximize potential client impact. The current “gold standard” for rating CBTs is rating recordings of therapy sessions, which is extremely time-consuming and requires a substantial amount of initial training. Although CBTs can vary based on the target disorder, one common element employed in most CBTs is the use of worksheets to identify specific behaviors and thoughts that affect a client’s ability to recover. The present study will develop and evaluate an innovative new approach to rate CBT fidelity, by developing a universal CBT scoring system based on worksheets completed in therapy sessions.

**Methods:**

To develop a scoring system for CBT worksheets, we will compile common CBT elements from a variety of CBT worksheets for a range of psychiatric disorders and create adherence and competence measures. We will collect archival worksheets from past studies to test the scoring system and assess test-retest reliability. To evaluate whether CBT worksheet scoring accurately reflects clinician fidelity, we will recruit clinicians who are engaged in a CBT for depression, anxiety, and/or posttraumatic stress disorder. Clinicians and clients will transmit routine therapy materials produced in session (e.g., worksheets, clinical notes, session recordings) to the study team after each session. We will compare observer-rated fidelity, clinical notes, and fidelity-rated worksheets to identify the most effective and efficient method to assess clinician fidelity. Clients will also be randomly assigned to either complete the CBT worksheets on paper forms or on a mobile application (app) to learn if worksheet format influences clinician and client experience or differs in terms of reflecting fidelity.

**Discussion:**

Scoring fidelity using CBT worksheets may allow clinics to test fidelity in a short and effective manner, enhancing continuous quality improvement in the workplace. Clinicians and clinics can use such data to improve clinician fidelity in real time, leading to improved patient outcomes.

**Trial registration:**

ClinicalTrials.gov NCT03479398. Retrospectively registered March 20, 2018.

## Background

Decades of research has demonstrated that cognitive behavioral therapies (CBTs) are effective for a wide variety of psychiatric problems and diagnoses [1]. Given this strong evidence base, CBT is cited as a first-line treatment in treatment guidelines for a variety of mood and anxiety disorders [2, 3] as well as for posttraumatic stress disorder (PTSD) [4, 5]. Numerous national, state, and regional mental health systems are implementing CBTs, requiring clinicians to offer them to their clients as clinically appropriate [6, 7]. To date, these efforts have largely focused on provider training and outcome monitoring, with less emphasis on ongoing quality assurance [8, 9].

Decreases in CBT quality can reduce both consumer access to evidence-based psychosocial treatments (EBPTs) and intended symptom improvement [9]. The possibility of “voltage drops” in effectiveness in non-research settings is therefore of great concern to researchers and policymakers [10]. It is important to monitor treatment quality as well as client characteristics and outcomes to learn whether the treatments are being delivered as intended and to understand reasons for potential differences in effectiveness or engagement [11]. Some research suggests that many providers do not implement EBPTs with fidelity [12–14], and a recent study determined that there was no relationship between self-reported primary cognitive behavioral theoretical orientation and observer-rated CBT competence [15]. In light of such research, ongoing quality monitoring and support is a key component in EBPT implementation and sustainability models [16–19]. Furthermore, articulates, policymakers, healthcare administrators, insurance providers, consumers, and other stakeholders need feasible methods of assessing the quality of services that are being delivered.

Efficient, scalable, and non-invasive methods of identifying what occurs in psychotherapy sessions remain elusive, yet they are critical to supporting and evaluating implementation outcomes. Empirically validated fidelity monitoring and support strategies are not yet in place in most healthcare systems [4, 6, 20]. Instruments developed to rate CBT fidelity are typically based on observation. While considered the “gold standard” in psychotherapy outcome research, observation is time- and labor intensive and not feasible in many practice settings [21]. Furthermore, scalable strategies to understand fidelity in practice is necessary, because for many psychotherapies, the link between observer-rated fidelity to session elements is not entirely clear and may differ based on the population characteristics. A recent meta-analysis demonstrated no overall link between observer-rated fidelity and symptom change across a range of treatments and disorders. Notably, though, in the analyses for many studies included in the meta-analysis, aggregated fidelity across the protocol introduced temporal confounds [22]. When analyses were conducted to avoid the confound and establish the temporal precedence of fidelity, two aspects of fidelity, adherence to the protocol, and competence (skill of delivery) in early CBT sessions were associated with subsequent decreases in depression [22]. Later research suggested that fidelity to key aspects of the treatment cognitive processing therapy (CPT; a CBT for PTSD), as opposed to prescribed session elements, was associated with symptom change [21, 23]. Thus, research on session fidelity or quality must establish temporal precedence of these factors to understand relationships between fidelity and symptom change in practice and must also examine strategies that emphasize the quality of delivery of critical treatment elements rather than fidelity to session components.

Researchers have also discovered limitations to existing indirect methods of monitoring fidelity, although they are sometimes used for pragmatic reasons [21]. Clinician self-reports of fidelity (e.g., checklists) appear to correspond only modestly with observer or client fidelity ratings [9, 12, 15, 24–26]. Both our preliminary work and published literature [27] indicate that clinicians (1) perceive adherence checklists as adding to an already high paperwork burden, (2) may not complete them as directed, and (3) may over- or underreport use of prescribed treatment elements. Literature on medical record review, checklists, and clinical progress notes to assess fidelity is mixed [28], and very little is specific to mental health [25, 28, 29]. One study indicated that record review may be a valid method of assessing clinician behavior [30], but research suggests that clinical progress notes convey poor estimates of frequency or intensity of EBPT techniques [30, 31]. Thus, conclusions about the interventions being delivered, and their quality, that can be drawn from self-report or clinical records may be limited.

While manualized CBTs exist for a wide variety of mental health conditions, a common element is the use of worksheets to teach and support client CBT skill development. Diagnosis-specific and transdiagnostic CBT protocols emphasize a set of core CBT elements, targeting clients’ behaviors and thoughts to reduce their symptoms. Both the behavioral and cognitive components of CBTs have been shown to impact symptom change for depression, anxiety, and PTSD [1, 32–35]. Worksheets are used in session to schedule specific behavioral activities and assess their impact on mood, anxiety, or sense of mastery. They are also used to guide one through the processes of cognitive restructuring, which helps clients learn to identify and challenge their maladaptive beliefs and generate balanced alternative thoughts [36, 37]. Assessing the quality of the worksheets that are completed with clinician guidance in sessions may therefore be a pragmatic and valid strategy to assess CBT quality. Thus, using worksheets completed in session to assess treatment fidelity may convey advantages over time-intensive observer ratings and imprecise self-reports of session content.

Another advantage of using worksheets to assess fidelity is that CBT worksheets are accessible and easily transmitted. They are available in paper form and through mobile technology that is accessible to people with disabilities (e.g., hearing- or vision-impaired). The majority of adults in advanced economies, and over half in emerging economies, own smartphones [38, 39]. Mobile applications (apps) are increasingly being used in CBT sessions, making transmission for real-time quality assessment feasible. Worksheets have been adapted for lower levels of literacy, multiple languages, traumatic brain injury, and other factors. Thus, it is possible to tailor worksheets that fit client needs and tailor strategies for collection and rating for different settings. However, the quality and feasibility of data collection may vary across formats and settings. For example, app worksheets may be more legible than handwritten data but may also be briefer or less detailed due to difficulties in typing on a phone. We propose to refine and test a unique method of assessing treatment quality through worksheets generated through routine clinical procedures. Specifically, we aim to (1) develop a scalable general CBT quality measure based on work samples rather than self-report or observation and (2) to evaluate the reliability, validity, and feasibility of different strategies for collecting these materials (e.g., mobile apps vs. paper worksheets).

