### Data collection and research strategy summary

After the development of the scoring system, we will prospectively collect data in a variety of settings, with clinicians (*n* = 120) who have varying levels of experience and expertise with CBT. We will collect data on clinician, client, and organizational characteristics that may impact the assessment of psychotherapy quality. We will collect worksheets, symptom measures, clinical notes with checklists of CBT strategies embedded within them, and therapy session recordings for participating clients. They will be provided to the investigators using secure, Institutional Review Board (IRB)-approved modes of data transmission that have been used successfully in our previous research [44–47].

Participating clients will be randomized into one of two different worksheet formats—app version or paper form (content is the same, mode of completion and data transmission differs). Raters will access the copies of the worksheets, or the mobile app dashboard, and score the worksheets. Clinicians, administrators, supervisors, and clients will be interviewed to assess perceptions of the quality assessment strategies and to determine feasibility, and these data will be analyzed using qualitative strategies.

The variety of worksheets and data capture sources (apps, paper forms) will allow assessment of clinician and client preferences, the degree of detail and completion required for accurate quality assessment. This strategy will allow us to answer several questions through our statistical and qualitative analyses. Analyses will be conducted to answer questions and test hypotheses regarding (1) the reliability and factor structure of the measure, (2) associations between the quality measure and subsequent symptom change (the primary outcome), (3) the concurrent validity of the measure, (4) whether the measure performs better than adherence checklists embedded in clinical notes, (5) whether different formats (apps vs. paper forms) have different concurrent or predictive validity, and (6) the feasibility, burden, satisfaction, and time requirements for the worksheets vs. the adherence checklists.

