#### Raters and scoring

We will apply the rating system that is refined in the first phase of the study to worksheets that are collected during the entire course of the study. The scoring rules (including decision rules for each session) and scoring algorithms are embedded in an electronic database for app and paper copies. The cadre of raters will include postdoctoral fellows from each system and bachelor’s level research assistants, and some are able to rate sessions and worksheets in Spanish. They will be trained to use the measure and to become familiar with all decision rules, and new decision rules may be identified during this training process. These sessions will be evenly distributed between raters. A subset (10%) will be rated by a second time (1 week after the first rating) to assess test-retest reliability. Furthermore, participating systems will nominate one person (whoever would be in a position to monitor quality) to receive brief training and rate 10 sessions to determine feasibility of training system/clinic-level quality monitors. They will be interviewed regarding potential for implementation within their setting. A randomly selected subset (20%) of the worksheets will be rated by CBT experts and compared with our raters. To score the adherence checklists embedded in the clinical notes, we will score the proportion of CBT elements that are checked off by clinicians.

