#### Reliability

We will examine correlations between the subset of worksheets that are rated twice to examine test-retest reliability. Next, we will compute estimates of internal consistency reliability for hypothesized CBT domains (e.g., identifying thoughts and feelings, cognitive restructuring, behavior planning and tracking) in the form of Cronbach’s alphas and retain domains with an alpha of .70 or above. We will calculate intraclass correlations (ICCs) for the total measure and for each content domain, using a random effects model to estimate the reliability of rater judgments [67]. Per established conventions and prior research [68], we will apply a minimum criterion ICC = .60 (“good”) [69] to indicate acceptable agreement. We will also compare bachelor’s level raters’ scores to expert rater scores to assess the degree of agreement, to determine a level of expertise required for rating.

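### Aim 2 promises the reliability of app versus paper worksheet collection, but the listed analyses compare the formats only on validity and estimate reliability without a split by format

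*Protocol article*

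**What the plan says.** All references are to the protocol article.

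- **Aim.** The Background states that the study will "to evaluate the reliability, validity, and feasibility of different strategies for collecting these materials (e.g., mobile apps vs. paper worksheets". The Discussion restates the aim with the same three properties. The Background also gives reasons why the formats may differ: typed entries may be easier to read than handwriting, but shorter or less detailed.
- **Analysis questions** (Data collection and research strategy summary). Question 1 is "the reliability and factor structure of the measure". Question 5, the one on format, is "whether different formats (apps vs. paper forms) have different concurrent or predictive validity". Question 6 covers feasibility, burden, satisfaction and time.
- **Reliability section.** Test-retest: "We will examine correlations between the subset of worksheets that are rated twice to examine test-retest reliability". Rater agreement: "We will calculate intraclass correlations (ICCs) for the total measure and for each content domain", for which "we will apply a minimum criterion ICC = .60". Cronbach's alpha is computed by hypothesised domain, and bachelor's-level raters are compared with experts. Format is not mentioned.
- **Raters and scoring.** "A subset (10%) will be rated by a second time (1 week after the first rating"; a random 20% of worksheets is also scored by CBT experts. Neither subset is described by format.

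**The concern.** The aim names reliability, validity and feasibility of the collection strategies. The analyses follow up two of these by format and leave out the third. Legibility and level of detail, the article's own reasons to expect a format difference, bear directly on whether two raters, or one rater on two occasions, give the same score.

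A single reliability estimate over both formats mixes their error variances, so it can look adequate while one format is clearly worse. The study would then report that the measure is reliable without showing that this is so for app and for paper. A programme choosing a format would lack one of the three pieces of information that the aim promised.

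**Working it through.** **1. Where format enters the analyses.**

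| Property in aim 2 | Analysis by format | Section |
|---|---|---|
| Validity | Question 5; effect sizes and variance explained, app vs paper; Fisher r-to-z on correlations with observer ratings | Data collection and research strategy summary; Analyses; Comparisons of quality measures |
| Feasibility | Transmission time, satisfaction and stakeholder views, app vs paper | Interviews and assessment of stakeholder perspectives |
| Reliability | None listed | Reliability |

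**2. Can an overall ICC hide a weak format?** The article's .60 is a fixed criterion, so there is no derived figure to reproduce. Assume equal numbers and equal mean scores in the two formats, with ICCs of .80 and .50. The article does not supply these values.

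- *Equal true variance (set to 1).* The error variance is (1 − ICC)/ICC: .20/.80 = .25 and .50/.50 = 1.00. The mean is .625. Overall ICC = 1/(1 + .625) = .615.
- *Equal total variance.* Overall ICC = (.80 + .50)/2 = .65.

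Both exceed .60 although one format stands at .50. The result depends on the variance model. For ICCs of .70 and .50, equal total variance gives .60, just meeting the criterion. Equal true variance gives error variances of .429 and 1.00, mean .714, and 1/1.714 = .583, which misses it. Under equal true variance, a format at .50 needs the other at .75: errors .333 and 1.00, mean .667, and 1/1.667 = .600.

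**3. Do the planned ratings support a split?** Inputs: 360 clients (Client inclusion criteria) and six observations per client (Sample size justification). Assumptions: 1:1 allocation, one scored session per observation, no clustering.

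- Sessions: 360 × 6 = 2,160.
- Test-retest subset: 10% = 216, or 108 per format.
- Expert-rated subset: 20% = 432, or 216 per format.

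Approximate 95% intervals use Fisher's z with standard error 1/√(n − 1.5):

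| True value | n = 108 (test-retest) | n = 216 (expert-rated) |
|---|---|---|
| .50 | .345 to .629 | .393 to .594 |
| .60 | .465 to .708 | .507 to .679 |
| .70 | .590 to .785 | .625 to .762 |

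The two columns serve different purposes. The 10% subset supports the test-retest correlation. The .60 criterion belongs to agreement between raters, for which the expert-rated 20% is the larger planned source of scores by different people. With 216 per format, an ICC of .50 or .70 would have an interval that excludes .60; values nearer .60 would not.

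**The case against.** **The article condenses a fuller plan and never says that the formats will be pooled.** This is true, and format is recorded, so a breakdown remains possible. A reader might infer that the study cannot answer the reliability part of aim 2; the text does not go that far. But the article does spell out its format comparisons and names validity alone, and it spells out the units for reliability (total, domain, rater level) without format. That is a mismatch between a twice-stated aim and the listed analyses, and more than an omitted detail.

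**The .60 value is not a rule for adopting a format.** This stands. A reader might infer that a format below .60 would be formally accepted because the overall ICC passes. The article uses .60 only to describe acceptable rater agreement. Its guidance on choosing a strategy rests on associations with outcome, correspondence with observer ratings, and programme needs.

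**The validity comparisons would expose a noisy format.** In part. Unreliable scores weaken correlations with observer ratings and with outcome. But this is indirect, the observer comparison uses only the 10% of recordings that observers rate, and it tests a difference without any reliability criterion.

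**The example ICCs are invented.** They are. The preliminary ICCs for clinician competence were .68 to .90, all above .60, although those for client skill began at .55. Those figures concern CPT worksheets and are not given by format, so they do not settle the matter. A reader might also infer that both formats could fall short while a difference in mean score lifts the overall ICC over .60. That is arithmetically possible: with .50 in both and a 1 SD difference, (.50 + .25)/(1 + .25) = .60. Nothing in the article supports a shift of that size, and it describes the content as the same in both formats.

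**Conclusion.** The point holds as a mismatch between aim and analysis. Reliability by format is promised in the Background and the Discussion, is missing from the format question, and is not among the units in the Reliability section. The numerical examples show only that an overall ICC of about .615 to .65 can coexist with one format at .50. They do not show that this is likely. The precision figures rest on equal allocation, one scored session per observation and independent sessions; clustering within clients and clinicians would widen the intervals. The consequence is limited to aim 2. The primary analysis of quality and symptom change, and the power calculation for it, do not depend on this.

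**What to change.** 1. In the Reliability section, also report the inter-rater ICC, the test-retest correlation and Cronbach's alpha separately for app and paper worksheets, each with a confidence interval, together with the difference between formats.
2. Read the inter-rater ICC against .60 within each format as well as overall.
3. Add reliability to question 5 in the Data collection and research strategy summary.

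If reliability by format is not intended, remove it from aim 2 in the Background and the Discussion.

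The cost is analysis wording and a few more rows in a table, with no additional ratings. The intervals per format are wider than the overall one, so a format with an ICC close to .60 should be reported as uncertain and not as a pass or a failure.

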### Preliminary work

#### Research on worksheet quality

In a preliminary study, we developed a method to assess fidelity to CPT by coding the level of adherence and competence reflected in worksheets that were completed in treatment sessions [40].

#### Reliability

Inter-rater reliability was high (ICC = .68 to .90) for clinician competence on different worksheets. It was adequate to almost perfect (ICC = .55 to .92) on ratings of client skill in completing worksheets independently.

#### Convergent validity

Observer-rated competence on full sessions were not significantly correlated with worksheet ratings (*r*_*pb*_ = .278, *p* = .068), but we found high (Spearman rank) correlations between our worksheet rating method and observer ratings for worksheet-related CBT elements (e.g., cognitive restructuring, *r*_*pb*_ = .823; *p* = .000). Similarly, correlation between observer-rated adherence (*n* = 44 sessions) and adherence scores based on worksheets was low for full sessions (*r*_*pb*_ = .062, *p* = .68) but high for worksheet-related items (*r*_*pb*_ = .808; *p* = .000).

